**Methods:**

In a cluster-randomised trial including 40 general practices, that participated until 2009 in the ADDITION Study, 150 T2DM patients 60–80 years, known with T2DM for 8-15 years, will be included. Practices are randomised a second time, i.e. intervention practices in the ADDITION study could be control practices in the current study and vice versa. For the GPs from the intervention group a 2-hour training in SDM was developed as well as a decision support tool to be used during the consultation. GPs plan the first visit with the patients to decide on the intensity of the treatment, personalised targets and the priorities of treatment. The control group will continue with the treatment they were allocated to in the ADDITION study. Follow-up: 24 months. The primary outcome is the proportion of patients who achieve all three treatment goals. Secondary outcomes are the proportion of patients who achieve five treatment goals (HbA1c, blood pressure, total cholesterol, body weight, not smoking), evaluation of the SDM process (SDM-Q9 and CPS), satisfaction with the treatment (DTSQ), wellbeing and quality of life (W-BQ12, ADD QoL-19), health status (SF-36, EQ-5D) and coping (DCMQ). The proportions of achieved treatment goals will be compared between both groups. For the secondary outcomes mixed models will be used. The Medical Research Ethics Committee of the University Medical Centre Utrecht has approved the study protocol (Protocol number: 11-153).

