## Methods

### Study design and setting

The OPTIMAL study is a cluster-randomised trial with randomisation at practice-level and two years follow-up. We developed an intervention to promote SDM with a decision support tool based on the results of the above mentioned ADDITION-Europe study. Since for an optimal SDM approach physicians should have some experience with all treatment options, patients are recruited from the 79 general practices that participated in the ADDITION study [29]. For the OPTIMAL study practices are randomised again (Figure 1). GPs in the intervention group were trained in SDM (see further).

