Participants in both groups will be asked to complete and return the following questionnaires baseline and after 24 months at home.the Diabetes Treatment Satisfaction Questionnaire (DTSQ) [30] which includes 8 items; scores range from 0 (very dissatisfied) to 6 (very satisfied), totally from 0 to 48. The DTSQ is reliable, valid and sensitive to change in diabetes patients [30];the Audit of Diabetes Dependent Quality of Life (ADD QoL-19), which measures the perceived impact of diabetes on the quality of life; it includes 19 items, ranging from -3 to 3 on different questions, with 0 as the neutral score. Scores below 0 reflect a negative influence of the item on quality of life, and all above 0 reflect positive influences. The impact scores are weighted (impact rating x importance rating), so the actual scores per item can range from -9 to 9. The ADDQoL-19 has good psychometric properties and provides clinicians and researchers with a useful tool for comprehensively assessing quality of life in adults with T2DM [31];the Well-Being Questionnaire (W-BQ12) that consists of 12-items in three 4-item subscales: negative well-being (item 1-4, higher score reflects a greater sense of negative well-being), energy (items 6 and 7 are reversed, and then together with 5 and 8 form the total amount of energy) and positive well-being (items 9-12, the higher the score the greater the sense of positive well-being). The total score ranges from 0 to 36 and is called the general well-being score. Higher scores indicate a higher overall sense of well-being [32];the European Quality of Life (EQ-5D) questionnaire, that covers 5 dimensions (mobility, self-care, usual activities, pain/discomfort and anxiety/depression) and a Visual Analogue Scale (VAS) where respondents can rate their health. Item scores range from 1-3, and a 5-digit health profile is formed, placing the 5 numbers behind each other. It is a well-validated, reliable and responsive instrument for health measurement in patients with a wide range of medical conditions. Values found in the UK have been validated for the Netherlands [33-35];the Short Form-36, a validated 36-item instrument for the self-evaluation of health status with eight subscales: Physical Functioning (10 items), Role Physical (4 items), Bodily Pain (2 items), General Health (5 items), Vitality (4 items), Social Functioning (2 items), Role-Emotional (3 items) and Mental Health (5 items). These scales can be summarised in Physical Health and Mental Health. The 36 items differ in the scoring ranges. The Dutch version has proved to be a practical, reliable and valid instrument [36,37];the Diabetes Coping Measurement Questionnaire (DCMQ), consisting of 21 items in 4 subscales: spirit coping, avoidance coping, passive resignation coping and diabetes integration coping. Overall scores range from 7 to 35. The items are measures on a 5-point Likert scale, ranging from 1 (“disagree”) to 5 (“agree strongly”) or the other way around from 1 (‘I strongly agree’) to 5 (I ‘disagree’). Higher scores on tackling spirit and diabetes integration indicate more adaptive coping. Higher scores on passive resignation and avoidance indicate poor coping [38].

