### Sample size

As stated in the Introduction, only 10-15% of T2DM patients achieve all three treatment targets for both HbA1c, lipids and blood pressure. We estimate the percentage of patients that already has reached three targets at the start of the study will be approximately 10%. We hypothesise that in the OPTIMAL study, after two years of follow-up, the intervention group will show an increase of this percentage until 30% (about 10% increase per year), whereas in the treatment-as-before-group this percentage will stay at 10%. Assuming a two-sided significance level of 5%, with alpha 0.05 and power of 80% and with a drop-out of 10%, 65 patients will be needed in each treatment group (Department of Statistics Sample Size Calculator, University of British Columbia). Because the OPTIMAL study is a cluster randomised study the sample size will require an correction for the cluster effect. The used correction factor is equal to [1 + (m - 1) r], where ‘m’ is the total amount of eligible patient per practice (approximately 6), and ‘r’ the within-cluster correlation coefficient. For ‘r’ we use a within-cluster correlation coefficient of 0.025, based on the cluster correlation found in the ADDITION-Europe study. When taken the cluster effect (1.125) in to account, 73 patients per group are needed.

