### Statistical analyses

Intention-to-treat analyses (ITT) will be performed to examine between-group differences. Generalized linear models will be used to correct for clustering at practice level. The proportions of achieved treatment goals of HbA1c, blood pressure, LDL-cholesterol within each study group will be estimated by calculating relative risk. The same applies to the difference between groups in the proportion of patients which achieved all the five above mentioned treatment goals. A p-value of <0.05 is considered statistically significant. To identify patients who show better results after the SDM process, the analysis for the primary outcome will be repeated with taken into account interaction of SDM with age, gender, education level, duration of diabetes and comorbidities. Within and between group differences in treatment satisfaction, perceived quality of life, health status, well-being, and coping style between baseline and 24 months follow-up will be analysed by using paired t-tests and mixed models respectively. We will add random effects for patient and practice.

The SDM-Q9 will be analysed in the intervention group by using paired t-tests. Mixed models will be used to study the between groups differences after 24 months. We will add random effects for patient and practice.

To evaluate the SDM proces, the tapes will be evaluated by two independent observers by making use of the SDM-Q9.

The Medical Research Ethics Committee of the University Medical Centre Utrecht has approved the study protocol (Protocol number: 11-153).

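### As normally read, the two-visit mixed model for the patient-reported outcomes drops practice out of the arm difference in change, so any practice-level clustering of change is missing from the standard error

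*Protocol article*

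**What the plan says.** The article's Study design and setting section fixes the unit of randomisation: "The OPTIMAL study is a cluster-randomised trial with randomisation at practice-level and two years follow-up". Under Measurements, data collection, the satisfaction, quality-of-life, well-being, health-status and coping questionnaires are given twice: "Participants in both groups will be asked to complete and return the following questionnaires baseline and after 24 months at home". Each patient therefore supplies at most two scores per instrument.

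Under Statistical analyses, the target is a change: "Within and between group differences in treatment satisfaction, perceived quality of life, health status, well-being, and coping style between baseline and 24 months follow-up". Within-arm change is assigned to paired t-tests and the between-arm comparison to mixed models: "24 months follow-up will be analysed by using paired t-tests and mixed models respectively. We will add random effects for patient and practice". The article does not say whether the practice effect is an intercept or may vary by visit. It also does not say whether baseline is an outcome row or a covariate, or whether the arms are constrained to share a baseline mean.

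The planned size is given in the abstract: "In a cluster-randomised trial including 40 general practices, that participated until 2009 in the ADDITION Study, 150 T2DM patients". For clustering, the Sample size section states that "we use a within-cluster correlation coefficient of 0.025".

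**The concern.** A random intercept for practice adds the same amount to a patient's baseline score and 24-month score. The between-arm question is about the difference between those two scores, so that amount subtracts out. What matters for a practice-randomised comparison of change is whether change itself is alike within a practice. This is plausible here, because training, the decision tool and the follow-up decisions all act through the GP. A model with patient and practice intercepts has no term for it.

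The analysis would then look adjusted for clustering while, for this contrast, treating patients' changes as independent. At stake are the intervals and tests for research question 2. The point concerns the between-arm mixed model, not the within-arm paired t-tests.

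**Working it through.** **Inputs from the article.** 150 patients in 40 practices, so 150/40 = 3.75 per practice (abstract). About 6 eligible patients per practice and a within-cluster correlation of 0.025 (Sample size). Two scores per patient (Measurements, data collection).

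**Assumptions, not in the article.** Within-patient correlation of 0.6 for the worked standard error. ICC of change from 0 to 0.10.

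**The plan's own figures first.** Unpooled two-proportion formula: (0.1×0.9 + 0.3×0.7) × (1.96 + 0.8416)² / 0.2² = 59 per group. For drop-out, 59 × 1.1 = 64.9, so 65. Design effect 1 + (6 − 1) × 0.025 = 1.125, and 65 × 1.125 = 73.1, so 73. Both stated figures reproduce, and the point does not touch them.

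**Step 1: cancellation.** Write the score of patient i in practice j at visit t as fixed part + u_j + p_ij + e_ijt. The change is D_ij = fixed part + e_ij1 − e_ij0. Neither u_j nor p_ij remains, so Var(D) = 2σ²_e. With 75 patients per arm,

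SE(arm × time) = √(2σ²_e × 2/75).

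With total variance 1 and within-patient correlation 0.6, σ²_e = 0.4, so SE = √(0.8 × 2/75) = 0.146 SD. The practice variance does not appear in the formula, so the result is the same at a practice ICC of 0, 0.025, 0.1 or 0.2.

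A generalised least squares calculation in another layout (4 patients per practice, 19 practices per arm, patient and residual variance 0.5 each) gives 0.1622 at practice variances 0, 0.025, 0.1 and 0.3. In one simulated data set, the fitted mixed model's standard error (0.1383) equals that of an ordinary regression of change on arm that ignores practice (0.1383). A change-score model with a practice effect gives 0.1411.

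**Step 2: size if change does cluster.** With ICC of change ρ and m patients per practice, the true variance is 1 + (m − 1)ρ times the reported one. The actual two-sided error of a nominal 5% test is 2[1 − Φ(1.96/√(1 + (m − 1)ρ))].

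| ICC of change | m = 3.75: true/reported SE | actual error | m = 6: true/reported SE | actual error |
|---|---|---|---|---|
| 0 | 1.000 | 5.0% | 1.000 | 5.0% |
| 0.01 | 1.014 | 5.3% | 1.025 | 5.6% |
| 0.025 | 1.034 | 5.8% | 1.061 | 6.5% |
| 0.05 | 1.067 | 6.6% | 1.118 | 8.0% |
| 0.10 | 1.129 | 8.3% | 1.225 | 11.0% |

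Simulation of null trials (8,000 per setting) agrees. At ICC 0.025 the error is 5.9% with 4 per practice and 6.6% with 6. At 0.10 it is 8.9% and 10.8%. A test on practice-mean changes stays near 5% throughout.

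**Step 3: other readings of the same sentence.**
- *Arms constrained to equal baseline means.* The practice term cancels only in part: the standard error moves from 0.1405 to 0.1527 as practice variance goes from 0 to 0.3. It is still too small when change clusters: 0.147 reported against 0.1545 true at ICC 0.025 (6 per practice, 12 practices per arm).
- *24-month score alone.* The practice intercept carries the clustering. The patient effect merges with the residual and is redundant.
- *Practice effect allowed to vary by visit.* The problem does not arise.

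**The case against.** The strongest reply is that the article does not commit to the model criticised. It names random effects for patient and practice without the words only or intercept, and a practice-by-visit effect is itself a random effect for practice. A condensed article may leave that detail to a fuller document. The same random-effects sentence is also attached to the SDM-Q9 comparison, which is made after 24 months only, so the patient effect may be a stock phrase and not a sign of two rows per patient.

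This limits the point but does not remove it. The article does choose its random effects and does define the patient-reported comparison as a baseline-to-24-month difference. A separate patient effect has a function only with two rows per patient. An analyst who followed the text in the ordinary way would fit intercepts.

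Two stronger conclusions are tempting. A reader might infer that the specification fails on every reading. It does not: fitted to the 24-month score alone, it carries practice clustering and is merely untidy. A reader might also infer that the 5% error rate is exceeded for every score. That needs a non-zero ICC of change for every instrument, and the article reports none. Its 0.025 was adopted to size the binary primary outcome, so using it here is an assumption.

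The size objection also has force. The figure of 6 counts eligible patients; 40 × 6 = 240, not the planned 150. The 3.75 column is therefore closer to the stated trial, and the 11% figure needs both 6 per practice and an assumed ICC of 0.10.

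**Conclusion.** The point holds in a conditional form. With random intercepts, two scores per patient and an arm-by-time contrast, the practice effect drops out of the arm difference in change. It does so exactly with complete pairs and unconstrained baselines, and partly if baselines are constrained equal. Clustering of change is then left out of the standard error in a trial that randomises practices.

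The consequence depends on an ICC of change that the article does not give. It is nil at 0 and modest at 0.025 (true standard error 3% to 6% larger than reported). It becomes material only towards an assumed 0.10. The secondary patient-reported outcomes of research question 2 are affected; the primary analysis and the sample size are not. The wording should be changed because the present text invites the wrong model and the remedy is almost free.

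**What to change.** For each patient-reported score, state that the 24-month value will be modelled on arm and the patient's baseline score, with a random intercept for practice, no patient random effect, and small-sample degrees of freedom (about 40 − 2 = 38 at practice level). With one outcome row per patient, the practice intercept carries the clustering that matters. In the single simulated data set above, this model's standard error was 0.1304, against 0.1411 for the change-score model with practice.

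If the two-visit model is preferred, add a practice-by-visit random effect and say whether baseline means are constrained equal between arms.

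The cost is a change of analysis wording, with no new data. If the two-visit version is kept, intervals will be slightly wider than under the stated model wherever change clusters by practice.

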
A process evaluation of the shared decision making ability of the general practitioners will be measured in the intervention group at baseline and after 12 months, and in both treatment groups at 24 months. Both the patients and GPs will be asked to complete The Shared Decision Making Questionnaire, both the patient (SDM-Q9-patient) and GP (SDM-Q9-doc) version will be used to evaluate this process.

The Shared Decision Making Questionnaire (both SDM-Q9 versions) [39-41] includes 9 items with ratings from 0 (completely disagree) to 6 (completely agree); the total score ranges from 0 to 54. It is a continuous scale, and the questionnaire developers did not describe any thresholds for ‘bad’ or ‘good’ SDM. Over the last years the SDM-Q9 has become a frequently used instrument in clinical practice. It has been translated into several languages. Internal consistency has been assessed for the Spanish and Dutch version (Rodenburg-Vandenbussche S, Pieterse AH, Kroonenberg PM, Stiggelbout AM,et al.: Further validation of the SDM-Q-9 and SDM-Q-Doc: psychometric properties in Dutch patients from primary and secondary care. Submitted). Item discrimination parameters were above 0.4 for all but one item. An analysis of internal consistency yielded a Cronbach’s α of 0.88 [39]. The Dutch version is currently being validated [41]. A modified version of the Control Preferences Scale (CPS) is used to determine the experienced role of decision making of the GP and patient. The CPS measures at a 5-point Likert scale, and has shown good reliability and validity [41,42]. The original Control Preference Scale by Degner [41], was developed to measure preference for involvement and is one of the most commonly used instruments to assess preferred decisional role [41,42].

Subsequently, the GPs of both groups (the intervention group trained, the control group not) will audio- or videotape one of their yearly consultations with a T2DM patient. They can choose the consultation to be taped themselves. These tapes will be evaluated by two independent observers, making use of the SDM-Q9, to assess the extent to which the GP is likely to involve his/her patients in the diabetes treatment.

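### Within-group changes in the patient-reported outcomes and the intervention-arm SDM-Q9 are tested with paired t-tests that ignore practice clustering, so their standard errors are somewhat too small

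*Protocol article*

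**What the plan says.** All analysis statements are in the protocol article, Statistical analyses.

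- **Patient-reported outcomes.** Within- and between-group differences in satisfaction, quality of life, health status, well-being and coping "between baseline and 24 months follow-up will be analysed by using paired t-tests and mixed models respectively". The last word pairs the t-tests with the within-group comparisons and the mixed models with the between-group ones.
- **SDM-Q9, within group.** "The SDM-Q9 will be analysed in the intervention group by using paired t-tests".
- **SDM-Q9, between groups.** "Mixed models will be used to study the between groups differences after 24 months. We will add random effects for patient and practice".
- **SDM-Q9 timing** (Measurements, data collection). It is "measured in the intervention group at baseline and after 12 months, and in both treatment groups at 24 months". Controls therefore have one SDM-Q9 occasion. Patient and GP versions are both used.
- **Clustering.** Generalized linear models are to correct for practice-level clustering; that sentence directly follows the one on between-group differences. The Randomisation section makes the practice the unit of allocation, and the Sample size section takes a within-cluster correlation of 0.025 with about 6 eligible patients per practice.
- **Significance.** The section sets one threshold, p below 0.05.

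**The concern.** A paired t-test reduces each patient to one change score and treats those scores as independent. Patients of one practice share a GP, a practice team and, in the intervention arm, a GP who attended the same training session. If practices differ in how much their patients change, the scores are positively correlated within practice and the t-test understates its standard error.

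Neither clustering provision reaches these tests. The generalized linear model sentence concerns between-group differences, and a t-test has no random effects, so "We will add random effects for patient and practice" can apply only to the mixed models. The same patients are handled as clustered for one comparison and as independent for the next.

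What is at stake is the within-arm evidence. For the SDM-Q9 this carries some weight: controls have no baseline score, so the before-after test in the intervention arm is the only planned test of SDM-Q9 change. A p-value that is too small there overstates the evidence that GPs improved.

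A smaller matter is the patient random effect in the 24-month SDM-Q9 model. With one score per patient per version, it cannot be told apart from residual error.

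**Working it through.** **1. The plan's own design effect.** Sample size section: m = 6, ICC = 0.025. DE = 1 + (m − 1) × ICC = 1 + 5 × 0.025 = 1.125, and 65 × 1.125 = 73.1, so the stated 73 per group reproduces. The plan thus accepts a variance inflation for its primary comparison that the paired t-tests omit.

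**2. Cluster size.** The Abstract gives 150 patients in 40 practices, a mean of 150/40 = 3.75. The Sample size section gives about 6. Both are used.

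**3. Formulas.** With equal clusters, the true SE of a mean change is √DE times the paired-t SE, so the paired-t SE is too small by 1 − 1/√DE. The actual two-sided level of a nominal 5% test is 2 × [1 − Φ(1.96/√DE)]. Here ICC is that of the *change* scores.

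| Patients per practice | Change ICC | DE | √DE | SE too small by | Actual level |
|---|---|---|---|---|---|
| 3.75 | 0.025 (document) | 1.069 | 1.034 | 3% | 5.8% |
| 6 | 0.025 (document) | 1.125 | 1.061 | 6% | 6.5% |
| 3.75 | 0.1 (assumed) | 1.275 | 1.129 | 11% | 8.3% |
| 3.75 | 0.2 (assumed) | 1.55 | 1.245 | 20% | 11.5% |
| 3.75 | 0.3 (assumed) | 1.825 | 1.351 | 26% | 14.7% |

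Simulated change scores (40,000 runs) at ICC 0.025 gave 5.8% for 75 patients in 20 practices and 6.6% for 12 practices of 6, in line with the formula.

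**4. Would random intercepts cure it?** Write the score of patient j in practice i at time t as μ_t + b_i + p_ij + e_ijt. The change is (μ_1 − μ_0) + (e_ij1 − e_ij0). Both intercepts cancel, so the model treats changes as independent, just as the t-test does. In a simulation with 20 practices of 4 patients and change ICC 0.2 (200 runs), the median ratio of mixed-model SE to paired-t SE was 1.000, and rejection under no change was 13.5% against 13.0%. Adding a practice-by-time term c_it leaves c_i1 − c_i0 in every change from practice i, which is the correlation that has to be modelled.

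**5. The patient effect in the 24-month SDM-Q9 model.** With one score per patient, the variance of a score is practice + (patient + residual), and only the bracketed sum enters the likelihood. For 150 simulated scores with practice variance 5, the log-likelihood was −547.3509 for patient/residual splits of 0/95, 25/70, 50/45 and 90/5 alike. In the patient-reported outcome models there are two scores per patient, and the patient effect is identified.

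**The case against.** The best case on the other side has four parts.

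- **The documented inflation is small.** At ICC 0.025 the level moves from 5% to between 5.8% and 6.5%. This stands. The document gives no ICC for SDM-Q9 or for any change score, so the larger figures are only a sensitivity range. A reader might infer a high ICC because patients of one practice rate the same GP. That argument concerns score levels; a GP's stable level cancels from a change, and only differences between GPs in how much they change count. It also does not carry over to the patient-reported outcomes, which do not rate the GP.
- **SDM-Q9-doc.** A reader might infer that each GP completes the form for several patients, adding clustering. The article says only that patients and GPs complete the questionnaire. One form per patient is not stated, so nothing here rests on it.
- **The redundant patient effect is harmless.** A reader might infer that the 24-month model must fail or give a biased contrast. Neither follows. Whether the software reports a problem varies, and the practice effect and group contrast are unchanged. The effect would be identifiable if the intervention arm's baseline and 12-month scores entered the model, or if both versions were modelled jointly; the article states neither.
- **Different methods for description and for comparison are not a contradiction.** This is fair: the between-group mixed models carry a practice effect. But the paired t-tests are planned under a section-wide significance threshold, and their standard errors should fit the design.

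**Conclusion.** The point holds at a modest size. The paired t-tests omit practice clustering, and nothing else in the section supplies it. Under the plan's own ICC, assumed to apply to change scores, the standard error is about 3% to 6% too small and the actual level about 5.8% to 6.5%. Under assumed ICCs of 0.1 to 0.3 with 3.75 patients per practice, it is 11% to 26% too small and the level about 8% to 15%. The calculation assumes equal cluster sizes.

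The 24-month SDM-Q9 patient random effect is a specification slip without consequence for the estimated group difference.

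A reader might go on to doubt the trial's main result. The document does not support that: the primary outcome, the sample size and the randomised contrasts are untouched. Only secondary and process analyses are affected. The correction is still worth making, because it is cheap and the error bars are otherwise wrong in a known direction.

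**What to change.** Replace the paired t-tests with within-arm change estimates and 95% confidence intervals that allow changes to correlate within practice. Any one of these will do:

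- a random practice-by-time effect added to the mixed model, alongside the practice and patient intercepts;
- cluster-robust standard errors by practice, with a small-sample correction, since 40 practices leave about 20 per arm;
- a t-test on practice-mean changes.

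The wording should name the practice-by-time term or its equivalent, because a model with only practice and patient intercepts returns the paired-t standard error. The same applies to the intervention-arm SDM-Q9 at baseline, 12 and 24 months.

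Base conclusions on the between-group contrast wherever both arms have baseline data, which covers the patient-reported outcomes. For the 24-month SDM-Q9 comparison, use a practice random effect only, fitted separately for each version, or state that the intervention arm's baseline and 12-month scores enter the model.

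The cost is a change of analysis wording and no new data. Within-arm intervals widen by about √DE, some 3% to 6% at ICC 0.025, plus a little for having fewer degrees of freedom at practice level.
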